**Figure 3. f3:**
[figure not shown]
Tentative DAG to handle confounders in the analysis.

PM
_2.5_ Treatment Strategy:

Primary analysis: PM
_2.5_ will be modeled as an effect modifier (Heat × PM
_2.5_ interaction).

Secondary analysis: If significant interaction is not detected, PM
_2.5_ will be adjusted as a confounder in sensitivity models.

Justification: Both exposures may exert synergistic biological influences on maternal thermoregulation and hemodynamics.

Prespecified Interactions and Stratifications:

Interactions to be formally tested include:

Heat × PM
_2.5_ (synergistic effects on maternal hemodynamics), Heat × Site (climate adaptation differences), Heat × Season (acclimatization effects), Heat × Occupation (differential vulnerability by work environment), and Heat × Housing Quality (thermal protection efficacy).

Stratified analyses will be conducted by site (Gurugram, Puducherry, Chhattisgarh), recruitment season (warm vs. cool), occupation (high-risk vs. lower-risk), housing quality (traditional vs. modern materials), and gestational timing (early vs. mid vs. late pregnancy enrolment).

Mediation and Sensitivity Analysis Framework:

The study design facilitates mediation analysis through temporally aligned data collection, with personalized exposure monitoring, blood pressure measurement, biomarker sampling, and clinical assessment conducted synchronously at three points across pregnancy. This alignment strengthens the exposure → mediator → outcome temporal sequence and reduces bias from measurement misalignment.

To address unmeasured confounding, the analysis will consider negative control approaches using biomarkers or outcomes theoretically unrelated to the heat–hemodynamic pathway, supplemented by mediational E-values to quantify the magnitude of unmeasured confounding required to alter results. The multi-site structure enables leveraging geographic and seasonal variation as natural experiments to test mediation assumptions.

To correct for measurement error, data from multiple exposure and mediator sources (personal vs. area exposures, various physiological and biomarker indices) will support formal error correction procedures where feasible. Advanced methods will include longitudinal mediation models to address time-varying confounding and Monte Carlo sensitivity analyses to evaluate robustness under assumption violations. Overall, the analysis framework will balance methodological rigor with practical constraints, transparently reporting assumptions and limitations while ensuring clinically interpretable insights into heat-mediated pathways influencing pregnancy outcomes.

Integration and Synthesis:

Findings from mixed-effects, DLNM, and mediation analyses will together characterize trimester-specific, cumulative, and mechanistic pathways linking heat exposure to maternal and fetal outcomes. Model selection and validation will apply AIC/BIC criteria and cross-validation for optimal parsimony and performance. Confounder selection will remain DAG-informed, with false discovery rate (FDR) adjustments in high-dimensional biomarker analyses to control false positives.

Together, these analytic approaches will enable a nuanced understanding of how maternal heat exposure shapes physiological adaptation and pregnancy outcomes, while generating evidence to inform targeted interventions and policy frameworks aimed at protecting maternal and neonatal health in a warming climate.

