### Study setting

The three study locations were selected to represent distinct climate zones across India, each with unique environmental exposures relevant to maternal and child health. Gurugram is located within the Delhi National Capital Region (NCR) and experiences a
**semi-arid climate**, characterised by extreme temperature variations, with scorching summers, cold winters, and limited rainfall, resulting in prolonged dry spells and frequent heatwaves. Chhattisgarh represents a
**humid subtropical to tropical wet and dry climate**, marked by high humidity, hot summers, and a well-defined monsoon season, creating conditions of alternating intense heat and moisture. Puducherry, situated along the southeastern coast, exemplifies a
**tropical wet and dry climate**, with persistently high temperatures, elevated humidity, and pronounced monsoon periods, particularly during the northeast monsoon. These diverse climatic conditions provide a natural contrast in thermal environments, enabling the study to capture a range of heat exposures and their differential impacts on pregnancy-related outcomes across varying ecological contexts.

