**Site 2: Puducherry**

Pondicherry Institute of Medical Sciences (PIMS) is a multi-speciality hospital and teaching Institute in the Union Territory of Puducherry, South India. The hospital is funded by the Madras Medical Mission, a charitable organisation that offers healthcare services at subsidised rates. PIMS laboratory is National Accreditation Board for Testing and Calibration Laboratories (NABL) accredited in medical testing for Clinical Biochemistry, Clinical Pathology, Haematology, Histopathology, Microbiology & others. PIMS has established the Demographic Developmental Environmental Surveillance Site (DDESS) funded by the Department of Biotechnology, Government of India which consists of a population of over 56,000 across 24 villages in the districts of Pondicherry and Tamil Nadu. Approximately 90 women attend the antenatal clinic daily with 100 deliveries conducted monthly. Study participants will be recruited from these villages through community-based screening.

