**Site 3: Chhattisgarh**

Chhattisgarh Institute of Medical Sciences is a multispecialty hospital and the second largest public medical college in Bilaspur in Chhattisgarh. The department of Obstetrics and Gynaecology runs a busy clinical service with 70 to 80 women attending each antenatal outpatient clinic, daily admissions of 25 to 30 pregnant women and approximately 600 deliveries each month. The department also draws a large number of emergency referrals from rural areas of the district as well as neighbouring districts. The department of radiodiagnosis performs 15 ultrasound scans per day, with other cases performed in the private sector. Diagnostic services in imaging, biochemistry, pathology, and microbiology are available on-site, with approximately 15 antenatal ultrasound scans performed daily. Study participants will be recruited from the antenatal outpatient clinics at CIMS.

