### Statistical approach

The study team will implement a pre-specified Statistical Analysis Plan (SAP), finalized and published prior to database lock, to quantify associations between environmental exposures—heat, humidity, and ambient PM
_2.5_—and maternal, fetal, placental, and early lactational physiological outcomes. Analyses will follow a hierarchical framework (primary, secondary, exploratory) with clearly defined endpoints to manage multiplicity. Data will undergo standardized procedures for cleaning, validation, and coding. Patterns of missingness will be described, and multiple imputation will be applied where appropriate. All model assumptions (normality, collinearity, linearity) will be evaluated systematically.

Primary Analytical Framework – Mixed-Effects Models:

Given the longitudinal and multi-site design of the HiP-India study, mixed-effects models (LME, GLMM, GAMM) will constitute the core analytic approach.

Random effects: Site-level random intercepts will account for geographic and climatic clustering across Gurugram, Puducherry, and Chhattisgarh, while subject-level random intercepts and slopes will capture individual differences in heat-response trajectories.

Serial correlation: Autoregressive structures (e.g., AR(1)) will model correlations between repeated trimester-specific measurements.

Time-varying exposures: Trimester-specific heat exposure estimates will be modeled as time-varying covariates to assess both immediate and cumulative effects.

Model flexibility: Linear mixed models will be used for continuous outcomes (e.g., physiological measures, biomarkers), generalized linear mixed models for binary outcomes (e.g., preterm birth, SGA), and generalized additive mixed models where non-linear exposure–response patterns are expected.

Complementary Distributed Lag Non-Linear Models (DLNM):

DLNM will be employed to examine delayed and non-linear exposure–response relationships across gestation.

Lag structure: Lags will extend from enrolment through outcome ascertainment, capturing both short-term (≤28 days) and longer-term (up to ~20 weeks) effects.

Basis functions: Natural cubic splines with empirically derived knots will model non-linear exposure and lag responses.

Temporal alignment: Exposure windows will be aligned primarily by calendar date to preserve seasonal context, and secondarily by gestational age to identify sensitive developmental periods. Hybrid alignment approaches will also be considered.

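### Heat × Site cannot be read as climate adaptation: each climate zone has only one site, and a linear heat term could add a spurious interaction

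*Protocol article*

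**What the plan says.** In Statistical approach, under Prespecified Interactions and Stratifications, the interactions to be formally tested include "Heat × Site (climate adaptation differences". Heat × Season stands beside it and is assigned to acclimatisation. Analyses stratified by site are also planned.

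Study setting explains the choice of sites: "The three study locations were selected to represent distinct climate zones across India, each with unique environmental exposures relevant to maternal and child health". It adds: "These diverse climatic conditions provide a natural contrast in thermal environments". Gurugram is described by "extreme temperature variations, with scorching summers, cold winters, and limited rainfall", Puducherry by "persistently high temperatures, elevated humidity, and pronounced monsoon periods". No temperature figures are given.

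The site descriptions differ in how women are found. For Puducherry: "Study participants will be recruited from these villages through community-based screening". For Chhattisgarh: "Study participants will be recruited from the antenatal outpatient clinics at CIMS".

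On the shape of the heat effect, Statistical approach assigns linear mixed models to continuous outcomes and "generalized additive mixed models where non-linear exposure–response patterns are expected". It adds distributed lag models with natural cubic splines and a check of linearity. It does not say which form heat takes in the Heat × Site test, and it sets no condition, such as a common heat range, before a positive test is read as adaptation.

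**The concern.** Two separate things can make Heat × Site differ from zero when women in the three climates are equally adapted.

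The first is aliasing. With one site per climate, any feature of a site that changes the measured heat response appears as a climate effect. This follows from the design and needs no assumption about the data.

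The second is the heat range. A straight line fitted to a curve that is flat when cool and steep when hot has a slope that depends on where the data lie. A site that is always warm would then show a steeper slope than a site with cold winters, although the curve is the same at both.

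At stake is a conclusion that one climate's women tolerate heat better or worse. The protocol says its evidence should inform targeted interventions and policy, and prespecification would lend such a conclusion a confirmatory air.

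**Working it through.** **1. What varies by site besides climate**

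| Feature | Gurugram | Puducherry | Chhattisgarh | Where stated |
|---|---|---|---|---|
| Climate zone | semi-arid | tropical wet and dry | humid subtropical to tropical wet and dry | Study setting |
| Facility | secondary-care hospital | teaching institute | medical college hospital | Site 1–3 |
| Recruitment | not site-specific | village screening | antenatal clinics | Site 2, Site 3 |
| Also in GARBH-Ini | all women | not stated | not stated | Recruitment |
| Sample transport | liquid nitrogen | dry ice | dry ice | Table 2 |

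Three sites allow 3 − 1 = 2 between-site contrasts. Three climates use both, so none is left for the other rows. Transport matters for biomarkers: if it rescaled an assay, the heat slope for the sFlt-1/PlGF ratio, a primary outcome, would differ by site without any physiological difference.

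**2. The protocol's effect size, reproduced**

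Per group, n = 2 × (1.960 + 0.842)² / 0.23² = 297, or 594 in total, against about 600 stated. With 300 per group the detectable difference is 2.802 × √(2/300) = 0.229 SD. The stated 0.23 SD is right and is used below.

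For one site of 200 women split 100 v 100 (equal sites and an even split are assumptions), the detectable difference is 2.802 × √(2/100) = 0.396 SD. For the difference between two sites' effects it is 0.396 × √2 = 0.56 SD, about 2.4 times 0.23 SD.

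**3. Why different heat ranges matter**

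Illustration with assumed seasonal mean WBGT of 15 and 30 °C (Gurugram) and 25 and 30 °C (Puducherry), and one common curve that is zero up to 28 °C and rises by 1 unit per degree above it. Ignoring scatter within season, the line between the two means has slope (30 − 28)/(30 − 15) = 0.13 at Gurugram and (30 − 28)/(30 − 25) = 0.40 at Puducherry. The women are identical, yet the slope is three times as steep.

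**4. Size of the false signal**

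Simulated F-test of Heat × Site at the 5% level, with the true curve the same at every site. Settings: 200 women per site, half warm and half cool season, one outcome per woman, 800 runs per cell, and curves scaled so that the high v low heat contrast is 0.23 SD. Assumed cool/warm means in °C (Gurugram, Chhattisgarh, Puducherry): wide 15/30, 19/30, 25/30; moderate 18/29, 21/29, 25/30; within-season SD 2 to 3. In each cell, the first figure is without and the second with adjustment for season.

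| True common curve | Linear heat, wide | Linear heat, moderate | Common spline + Heat × Site (wide; moderate) |
|---|---|---|---|
| Hinge at 26 °C | 13.8%, 13.6% | 14.9%, 13.2% | 4.6%; 4.9% |
| Hinge at 28 °C | 16.0%, 18.4% | 23.2%, 24.8% | 6.0%; 5.1% |
| Convex quadratic | 10.4%, 9.0% | 8.8%, 8.8% | 5.9%; 4.5% |
| Linear (control) | 5.4%, 4.0% | 5.0%, 5.8% | 3.9%; 5.4% |

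With identical heat ranges at all sites, the curved responses gave 5–7%. A separate simulation at 0.23 SD and 600 women gave 7–19% with linear heat and 5–6% with a common spline. Together, the range is roughly 7–25%.

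Larger contrasts raise it: 27–79% at 0.5 SD. If the three trimester records per woman were fully independent (1,800 records, an upper bound), it would be 17–64% at 0.23 SD.

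**The case against.** The strongest objection is that the protocol does not commit to a linear heat term in this test. It provides additive mixed models, splines in the distributed lag models and a linearity check, and the functional form of an interaction is ordinary SAP content. This stands. A reader might infer that the test will signal adaptation when there is none. The documents do not support that. It requires a linear term, a curved response and different heat ranges, and the protocol gives no heat distribution, curve or number per site. A common smooth curve brings the rate back to about 5%.

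A reader might also infer that the study ignores the adaptation data it holds. It does not: Heat × Season already tests acclimatisation, though coarsely.

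The recruitment contrast is also less sharp than the two site descriptions suggest. The Recruitment section names both clinic staff and community health workers, the structured summary calls recruitment mixed, and eligibility is common to all sites.

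Finally, the study calls itself exploratory and promises to report its limitations, and nothing says that a positive test would be published as better adaptation.

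None of this answers the aliasing. A smooth model removes an artefact of functional form, but it does not create a second site in any climate.

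**Conclusion.** The concern holds in two parts of different strength.

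- **Unconditional:** Heat × Site cannot be attributed to climate adaptation, because climate and site coincide. The label in the protocol claims more than the design can identify, whatever model is used.
- **Conditional:** with a linear heat term and a curved common response, the false-positive rate is roughly 7–25% instead of 5% at 0.23 SD and 600 women. This rests on the assumed heat ranges, curve shapes and equal site sizes. It disappears if the response is linear and largely disappears if the sites' heat ranges coincide.

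The point concerns what may be concluded from one prespecified interaction. It does not touch the main heat effects. It should be corrected before the SAP is finalised.

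**What to change.** 1. In the protocol and SAP, replace the adaptation label on Heat × Site with between-site heterogeneity, and state that a positive test will not be interpreted as adaptation.
2. Test Heat × Site as a departure from a common non-linear heat curve, over the heat range that the sites share. The restriction is worth keeping beside the spline: in the worst simulated case (sharp hinge at 28 °C, 1.0 SD, 1,800 independent records, wide ranges) a spline-by-site test over the full range still rejected 18% of the time.
3. Optionally, as exploratory work, add a within-site interaction of heat with each woman's mean temperature over the preceding 30 days, from the satellite series already planned. This would refine Heat × Season as a test of short-term acclimatisation. It says nothing about long-term climate adaptation. It must also include the common flexible curve: with linear heat its false-positive rate at 0.23 SD was 8–61% in a check under assumed distributions, against about 4–7% with a common spline.

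The cost is wording and model specification, with no new data. The price is precision. Under the wide assumption, the shared range starts near 21 °C (25 − 2 × 2 at Puducherry, 15 + 2 × 3 at Gurugram), so nearly all of Gurugram's cool-season women would leave this comparison. The 0.56 SD detectable difference between two sites would then become larger still.

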## Study design

This will be a multicentre prospective cohort study enrolling pregnant women at 11–14 weeks of gestation and following them up until two weeks after birth. The study aims to capture detailed environmental, clinical, physiological, and biochemical data across key gestational windows, enabling a comprehensive assessment of the maternal and fetal response to heat exposure over time.

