### Recruitment

Potential participants will be identified by clinic staff deployed at each hospital antenatal care centre and community health workers from surrounding villages. Recruitment will be supported by routine screening during antenatal visits, community outreach, and engagement with local health workers to ensure adequate enrollment and timely identification of eligible women to meet the target sample size. The project staff will approach potential participants and provide verbal information about the project, along with the participant information sheet. To supplement the information about the project, the team will provide pamphlets at each site, briefly describing its aims and overall outline, including details about the home visits. For those with low literacy or a preference for oral or visual information, a short video will be shown to convey the same information in the local language, which can be viewed on the project member’s tablet computer. The participant information sheet will describe the project, outline the activities involved if they participate, and detail any potential risks and benefits. Participation in the study will not influence clinical care delivery in each site; however, if clinical conditions are suspected during any of the study assessments, women will be referred to the local obstetric team for review. Participants will have an opportunity to ask questions to the study team members.

An orientation to the study will also be conducted for the landlords for the participants who stay in rented accommodations to explain the nature of the environmental assessments. 

For women who are willing to participate, a dating ultrasound will be arranged within the next 7 days to confirm her pregnancy is (i) viable and the inclusion criteria as mentioned above. If the dating ultrasound report indicates a gestation period of less than 10 weeks, the participant will be invited back for another scan within the enrolment window period of 11- 13+6 weeks of gestation. The participant will be asked to provide written informed consent to participate in the study after confirmation of the inclusion criteria. It will be made clear that she can withdraw her consent at any time during the study, with the option also to remove any data collected up to that point if she wishes. As all participants at the GCH site will also be enrolled in the GARBH-Ini Cohort
^
7
^, participation in this study will require a separate consent.

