### Biospecimen and data collection methods

Each site will have a separate dedicated team of research physicians, study nurses, clinical & laboratory technicians and field workers. These site teams along with site and project managers will form a cumulative clinical research unit (CRU), who would be responsible for implementing all study-related procedures at the three sites.

Sample and data collection at the study sites, during home visits, or by telephone interviews will be conducted by the study nurses using electronic forms under the supervision of medically qualified and trained research physicians. The field workers are responsible for ensuring that participants adhere to the study follow-up schedule. A separate trained research team ensures compliance to follow-up schedules. Local research laboratory teams will collect all biospecimens, pre-processing will be carried out at each of the three study sites respectively and transported to THSTI for long term archival at the ISO20387 accredited biorepository facility following standard operating protocols to ensure sample integrity and quality.

After confirmation of eligibility and recruitment, women will undergo assessments at three time points during pregnancy corresponding with the three trimesters summarised in
Table 1 and
Table 2 respectively.

**Table 1. T1:** List of procedures and assessments at three time points during pregnancy corresponding with the three trimesters for the study participants.

	Start				Close out	
		N=600	N=600	N=600	N=600	N=100
Timepoint	t _-1_	t _0_ 11–14 weeks	t _1_ 18–22 weeks	t _2_ 30–34 weeks	t _4_ birth	t _5_ 0–16 days PN

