## Structured summary

Public title: Heat in Pregnancy – IndiaScientific title: Effects of extreme heat on maternal, placental and fetal physiology, lactation and newborn health in IndiaStudy design: Prospective cohort studyStudy population: Pregnant women enrolled in the first trimester in three sites: Gurugram, Chhattisgarh, PondicherrySetting: Mixed hospital and community-based recruitment sites in Gurugram, Chhattisgarh, Pondicherry during winter and summer monthsTarget sample size: 600 participants (300 in the summer group and 300 in the winter group)Intervention/exposure: Natural seasonal heat exposure (participants recruited in summer vs. winter months)Comparator/control: Women recruited in winter months serve as the comparator groupPrimary outcomes: Incidence of preterm birth (<37 weeks); birth weightSecondary outcomes: Gestational age, stillbirth, and other maternal/newborn health outcomesKey inclusion criteria: Pregnant women in 11–14 weeks, aged 18–45 years, residing in the area for at least 6 monthsKey exclusion criteria: Women with pre-existing chronic illnesses or those unlikely to remain in the area during follow-upStudy period: Expected recruitment from May 2023 to March 2026

Ethics approval: Approved by

1.Translational Health Science and Technology, Institute, Faridabad (THS 1.8.1/ (171)2.Gurugram Civil Hospital (GCH/EC/2021/1826/8.12.2023/28.1)3.Chhattisgarh Institute of Medical Sciences, Bilaspur (327/C.I.M.S/I.E.C/2024)4.Pondicherry Institute of Medical Sciences, Puducherry (RC/2024/08)5.The George Institute for Global Health, India (Project Number 31/2023)6.Sri Ramachandra Institute of Higher Education and Research (IEC/24/MAR/185/07)•Trial registration: Clinical Trials Registry of India (CTRI)-(CTRI/2024/12/078527), registered on 24/12/2024 open for 3 years.•Data sharing: De-identified participant data and metadata will be shared through Zenodo, a public repository:
**
10.5281/zenodo.16421773
**
•Funding source: Supported by the Wellcome Trust

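### The prespecified stratification by early, mid and late pregnancy enrolment cannot be run, because all women enrol at 11 to 13+6 weeks

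*Protocol article*

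**What the plan says.** In the protocol article, under Statistical approach (Prespecified Interactions and Stratifications), stratified analyses are planned by site, recruitment season, occupation, housing quality and "gestational timing (early vs. mid vs. late pregnancy enrolment".

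Enrolment is described in four places:
- **Inclusion criteria:** gestational age at recruitment from 11 weeks to 13 weeks 6 days by crown-rump length.
- **Study design:** a cohort "enrolling pregnant women at 11–14 weeks of gestation and following them up until two weeks after birth".
- **Recruitment:** a woman whose dating scan comes too early is "invited back for another scan within the enrolment window period of 11- 13+6 weeks of gestation".
- **Structured summary:** "Pregnant women enrolled in the first trimester in three sites".

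After recruitment, "women will undergo assessments at three time points during pregnancy corresponding with the three trimesters". Table 1 puts these at 11–14, 18–22 and 30–34 weeks, with N=600 at each.

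Timing of exposure is also handled elsewhere. For the mixed models, Statistical approach says: "Trimester-specific heat exposure estimates will be modeled as time-varying covariates to assess both immediate and cumulative effects". For the distributed lag non-linear models (DLNM), exposure is aligned first by calendar date and "secondarily by gestational age to identify sensitive developmental periods". The section on placental circulating biomarkers assigns the search for critical windows to DLNM and generalized additive models (GAM).

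**The concern.** A stratified analysis needs women in more than one stratum. Here the stratifier is gestational age at enrolment, which eligibility holds to three weeks of the first trimester. The analysis is positively stated in the article, so it is not a detail left to the statistical analysis plan. A plan that copies the line inherits an analysis with one group. A plan that silently replaces it departs from the published protocol.

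The line also matters because of what stands beside it. The maternal haemodynamic section hypothesises that the effect of heat on the circulation depends on gestational age at exposure, with one mechanism early and another in mid-to-late pregnancy. That is a question of effect modification by gestational window. The five interactions to be formally tested are heat with PM2.5, site, season, occupation and housing quality. Gestational window is not among them. Four of the five stratifiers (site, season, occupation, housing) have a matching interaction. Gestational timing is the one that does not, so it is the only item in that prespecified list aimed at timing, and it is defined on the wrong variable.

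**Working it through.** **1. The plan's own figures.** For 0.23 SD, two-sided 0.05 and 80% power, n per group = 2(1.960 + 0.842)²/0.23² = 297, or 594 in total, against about 600 stated. With 300 per group the power is 80.4% and the detectable difference is (1.960 + 0.842)√(2/300) = 0.229 SD. For attrition, 600/0.85 = 706, against 700 stated, which is close enough. The stratifier enters none of these, so the sample size is not affected.

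**2. The enrolment window in days.** From the inclusion criteria:
- lower limit 11+0 weeks = 11 × 7 = day 77
- upper limit 13+6 weeks = 13 × 7 + 6 = day 97
- length = 97 − 77 + 1 = 21 days

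**3. Overlap with each candidate stratum.** Overlap of [77, 97] with [a, b] = max(0, min(97, b) − max(77, a) + 1). The article does not define early, mid and late, so the usual trimester cut-offs of 14+0 weeks (day 98) and 28+0 weeks (day 196) are assumed.

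| Candidate stratum | Days | Overlap |
|---|---|---|
| First trimester | up to 97 | 97 − 77 + 1 = 21 |
| Second trimester | 98 to 195 | 97 − 98 + 1 = 0 |
| Third trimester | 196 onward | 97 − 196 + 1 < 0, so 0 |
| 18–22 week visit | from 126 | 97 − 126 + 1 < 0, so 0 |
| 30–34 week visit | from 210 | 97 − 210 + 1 < 0, so 0 |

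**4. Is there any other route in?** None is described. The re-invitation rule returns women to the same window. The two later visits are follow-up of women already enrolled.

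**5. Sensitivity to the cut-offs.** Any definition that puts mid and late pregnancy after 14 weeks gives the same result. Cutting the 21 days into thirds would fill three cells, but none would be mid or late pregnancy.

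**6. Which outcomes could carry a timing contrast?** From Table 1 and the measurement sections:
- **Repeated at all three windows:** urine specific gravity, core temperature, maternal haemodynamics including cardiac output, and maternal blood (hence sFlt-1/PlGF).
- **At 18–22 and 30–34 weeks only:** uterine artery Doppler.
- **Once only:** preterm birth and birth weight (at birth); cardiotocography (CTG), umbilical artery, middle cerebral artery (MCA) and cerebroplacental ratio (CPR), all in the third trimester.

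A heat-by-visit-window interaction can be estimated for the first group and, with two windows, for the second. It has no repeated outcome to act on in the third.

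**The case against.** The strongest reply is that the last word of the stratifier is a slip. Every woman is assessed in three trimester windows, so the authors very likely meant early, mid and late exposure or assessment. That is plausible, and it is why the remedy is small. It does not rescue the line: enrolment and exposure are different variables, and only one of them varies here.

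The second reply is that the critical-windows aim does not depend on this line. This stands. A reader might infer that a stated aim of the study is left without an analysis, and the article does not support that. It gives the aim to DLNM and GAM, models trimester-specific exposures in the core mixed-model framework, and aligns the DLNM to gestational age as a secondary step. Nowhere does it make the stratified analysis the route to that aim. What remains is narrower. A time-varying exposure with a single coefficient does not by itself test whether the heat effect differs between windows, and no listed interaction does so.

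The third reply is that placing all women in one stratum restates the eligibility rule and measures no bias or loss of power. That is correct, and none is claimed.

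**Conclusion.** Wrong as written. A prespecified stratified analysis is defined on a factor with one level: all of the roughly 600 analysed women are in the early stratum, with none in mid or late, so no contrast exists. This rests on the stated eligibility window and on mid and late meaning later than 14 weeks. The consequence is limited to this stratification and to the absence, among the listed interactions, of a test by gestational window. The main models, the adjustment set and the sample size stand. It should be corrected before the analysis plan is finalised, which the article places before database lock.

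**What to change.** Replace the stratifier with gestational window of exposure or assessment (11–14, 18–22 and 30–34 weeks), and state the analysis by type of outcome:

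- **Outcomes repeated across visits** (cardiac output, urine specific gravity, core temperature, sFlt-1/PlGF): add a heat-by-visit-window interaction to the mixed model, keeping the planned within-woman correlation. The windows are the same women measured again, so separate models by window should not be compared as if they were independent groups.
- **Uterine artery Doppler:** the same term, with the 18–22 and 30–34 week windows only.
- **Outcomes measured once** (preterm birth, birth weight, CTG, umbilical artery, MCA and CPR Doppler): use window-specific exposure terms, or the planned DLNM aligned by gestational age. For preterm birth, say how women who deliver before the 30–34 week visit are handled, since they have no exposure measurement at that visit.

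Add heat-by-gestational-window to the list of interactions for formal testing, so that the haemodynamic hypothesis has a named test. If no contrast by timing is wanted here, delete the stratifier and refer to the DLNM.

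The cost is a few lines of wording in the protocol and analysis plan. No new data are needed and the sample size does not change.
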